#### *Cost and cost effectiveness*

TCM costs will be calculated using a standard micro-costing (bottom-up) approach [41], and will be based on teacher and trainer salaries plus on-costs (employers national insurance and superannuation contributions) and appropriate capital, administrative and managerial overheads. Costs for NHS hospital contacts will be taken from NHS reference costs [42]. Nationally applicable unit costs will be applied to all community health and social care contacts [43], medications [44], crimes and criminal justice resources [45,46]. The costs of schooling and school based services will be taken from various sources including Ofsted reports (the UK inspectorate and regulatory body for schools in England; http://www.ofsted.gov.uk) and published documents [47,48].

Despite the often skewed nature of costs, mean costs will be compared using standard parametric tests and the robustness of the results confirmed using bootstrapping [49]. The advantage of this approach, as opposed to logarithmic transformation or non-parametric tests, is the ability to make inferences about the arithmetic mean, which is more meaningful from a budgetary perspective [50].

The primary economic evaluation will explore cost-effectiveness at the T3 follow-up. Cost-effectiveness will be measured initially in terms of the primary outcome measure (SDQ). Cost-effectiveness will be assessed using the net benefit approach [51]. Uncertainty around the cost and effectiveness estimates will be represented by cost-effectiveness acceptability curves [52,53]. A joint distribution of incremental mean costs and effects for the two groups will be generated using non-parametric bootstrapping to explore the probability that each of the treatments is the optimal choice, subject to a range of possible maximum values (ceiling ratio) that a decision-maker might be willing to pay for an additional unit of outcome gained. Cost-effectiveness acceptability curves will be presented by plotting these probabilities for a range of possible values of the ceiling ratio [54]. These curves are a recommended decision-making approach to dealing with the uncertainty that exists around the estimates of expected costs and expected effects associated with the interventions under investigation and uncertainty regarding the maximum cost-effectiveness ratio that a decision-maker would consider acceptable [53,55]. To explore the longer-term implications of TCM, data from the RCT will be extrapolated and supplemented with data from the literature using decision analytic modelling techniques [56], in line with methods used to model the long-term impacts of parenting interventions for the prevention of persistent conduct disorders in children [57].

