#### *Economic evaluation*

The economic evaluation will take a broad public sector perspective, including the use of all health, education and social care services, plus criminal justice sector resources and criminal activity. Data will be presented by sector to allow alternative perspectives to be considered separately. Economic data will be collected at T0, T1, T2 and T3; at baseline, information will cover the previous 6 months; at follow-up service use since the previous time-point will be recorded. The cost and cost-effectiveness of TCM compared to TAU will be analysed at the final follow-up point (T3) in terms of the child’s socio-emotional well-being.

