#### *Teacher completed measures on each child*

##### Strengths and difficulties questionnaire (SDQ [18])

The teacher-rated version of the SDQ is the *primary outcome**measure*. The SDQ is a brief, valid and reliable measure of socio-emotional competence that is widely used to assess mental health in childhood. It will be completed by teachers and by parents at all four time-points. The subscales, *behaviour, emotions,**overactivity/concentration, peer**relationships and**prosocial behaviour,* will allow the examination of particular aspects of well-being in isolation. Responses to the first four add to give a *Total Difficulties* score. Ratings of child distress and impact of difficulties on home life, friendships, classroom learning, and leisure activities combine to form the *Impact Scale*. Teacher SDQs will be cross-validated with parental SDQs, direct observation and the child view of school measure described below.

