### Economic resource-use data

#### *Parent completed measures*

##### Child and adolescent service Use schedule (CA-SUS) [27-29]

Resource-use information will be collected using the Child and Adolescent Service Use Schedule (CA-SUS), developed by one applicant (SB) in previous economic evaluations involving child and adolescent mental health populations [27-29]. Two versions of the CA-SUS will be used. Firstly, a brief self-report version to collect data on a limited set of key resource items (high cost and/or high use) from all parents at all four time points. Second, the full standard interview version of the CA-SUS will be used with a random sample of 50 parents in interview at T2 and T3 in order to validate and supplement the briefer self-complete version at all time points.

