Unadjusted analyses and analyses adjusted for important prognostic factors at the pupil level (e.g. child gender, year group and baseline SDQ score), cohort of recruitment and the school level (level of deprivation, urban versus rural status and whether involved in other emotional enrichment programmes) will be implemented. In a secondary analysis, interaction terms will be included to investigate possible differences in intervention effect (on the primary outcome SDQ score only) between pre-defined subgroups based on school and individual deprivation, low versus high baseline SDQ scores, length of teacher experience and year group. These sub-group analyses have been selected for a number of reasons. First, children experiencing socio-economic deprivation may benefit more than their more privileged peers. Second, previous work suggests that children with higher levels of difficulties experience the most benefit [10]. Third, teachers in our Feasibility Study suggest that newly-qualified teachers would gain the most from the course, and finally, there is a common belief that these interventions will have the biggest impact on younger children. The latter belief has focused research on very young children and this would be the only study to investigate TCM in children aged over seven years. P-values of 0.01 and less will be interpreted as providing evidence for interaction effects. Although the power to detect moderate subgroup interactions will be low, we are primarily interested in investigating the possibility of large quantitative interactions and not qualitative interactions where the direction of intervention effect differs between sub-groups. Demographic and baseline characteristics at the school and pupil level will be summarised using means and standard deviations (or medians and inter-quartile ranges) for quantitative characteristics and percentages for categorical characteristics.

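### The economic analysis is specified as a comparison of arm means with no baseline covariate, although T0 service use and T0 SDQ are collected; the cost is precision, not bias

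*Protocol article*

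**What the plan says.** Under Cost and cost effectiveness, the protocol article says that "mean costs will be compared using standard parametric tests and the robustness of the results confirmed using bootstrapping". It defends this choice against log transformation and non-parametric tests, because the arithmetic mean matters for budgets. For cost-effectiveness at T3, "Cost-effectiveness will be assessed using the net benefit approach", and "A joint distribution of incremental mean costs and effects for the two groups will be generated using non-parametric bootstrapping"; the acceptability curves come from that distribution. No covariate is named for any of these steps.

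The baseline data exist. Under Economic evaluation: "Economic data will be collected at T0, T1, T2 and T3; at baseline, information will cover the previous 6 months". The CA-SUS section describes "Firstly, a brief self-report version to collect data on a limited set of key resource items (high cost and/or high use) from all parents"; this version is used at baseline and at each follow-up. Of the SDQ, the article says: "It will be completed by teachers and by parents at all four time-points".

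Covariates are listed under Analysis of effectiveness. That section plans unadjusted analyses and analyses "adjusted for important prognostic factors at the pupil level (e.g. child gender, year group and baseline SDQ score"), together with cohort and school-level factors. It does not say which of the two is primary, and it does not list baseline service use or cost.

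**The concern.** Past service use is a natural predictor of later service use, and baseline SDQ of later SDQ. The trial collects both on all participating families, but the stated economic method gives neither a role in the comparison. Read plainly, the cost analysis is a two-group test of means and the cost-effectiveness analysis is a bootstrap of two-group differences. The article does list covariates where it intends them, and it lists none here.

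An acceptability curve turns the incremental estimates and their spread directly into probabilities. Avoidable variance in incremental cost or effect therefore makes the curve less decisive. The SDQ effect inside the cost-effectiveness result could also differ from the adjusted T3 SDQ effect in the effectiveness report.

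**Working it through.** **1. The plan's own figure.** Inputs from Proposed sample size: 40 schools per arm, 19 children per school at T3 (760 per arm), ICC 0.15, target effect 0.3 SD or 2 points.
- VIF = 1 + (19 − 1) × 0.15 = 3.7.
- Effective n = 760 / 3.7 = 205.4 per arm.
- SE of the T3 SDQ difference = √(2 / 205.4) = 0.0987 SD.
- Two-sided 5% power = Φ(0.3 / 0.0987 − 1.96) = Φ(1.08) = 0.86, or 0.851 from a t distribution with 78 df. The stated 85% is reproduced.
- With 34 schools per arm (Retention): 34 × 19 / 3.7 = 174.6, power 0.800. The stated 80% is reproduced.

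The article gives no precision figure for the economic comparison.

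**2. Gain from baseline adjustment.** With correlation r between the T0 and follow-up values, adjustment multiplies the SE by √(1 − r²), so the unadjusted interval is 1/√(1 − r²) times as wide. The article gives no r; the range is an assumption. The formula also takes r to be the same at pupil and school level.

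| Assumed r | √(1 − r²) | Unadjusted interval wider by | 1.96 × r × 0.0987 |
|---|---|---|---|
| 0.2 | 0.980 | 2% | ±0.04 SD |
| 0.4 | 0.917 | 9% | ±0.08 SD |
| 0.6 | 0.800 | 25% | ±0.12 SD |

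The last column is the 95% range of chance baseline imbalance carried into the unadjusted SDQ difference, against a target of 0.3 SD. It is the same loss seen from another side and should not be added to the widening.

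**3. Costs.** The widening depends only on r, so the third column applies unchanged. No cost ICC is given. For an assumed ICC of 0.01 to 0.15 the SE is √(2 × 1.18 / 760) = 0.056 to 0.099 SD of cost. The carried imbalance is then about ±0.02 to 0.04 SD at r = 0.2 and ±0.07 to 0.12 SD at r = 0.6.

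**4. Where r is likely to lie for the SDQ.** Under Design, children have new teachers in each follow-up year, so the T0 and T3 teacher ratings come from different people. At ICC 0.15, the variance of a school mean is 0.15 + 0.85/19 = 0.195 (in SD²), of which 0.15/0.195 = 77% lies between schools. Any part of this that is the T0 teacher's rating style does not carry forward to T3. This points towards the lower rows of r.

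**5. Why regression and not change scores.** T0 service use covers six months, while follow-up covers all time since the previous assessment, up to 30 months in total. A change in cost would compare unlike periods. Regression on T0 cost avoids this.

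**6. Why the remedy must mention schools.** If an adjusted model or its bootstrap treated children as independent, the SE would be too small by √VIF. That is √1.18 = 1.09 at an assumed cost ICC of 0.01 and √3.7 = 1.92 at 0.15. The true size of a nominal 5% test would be about 7% and 31%.

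**The case against.** The strongest objection is that this argues from silence in a condensed article. The economic section does not use the words raw or unadjusted, and it excludes no covariate. The sentence on parametric tests answers a question about skewed costs. Linear regression is itself parametric, and net benefit can be run as a covariate-adjusted regression. An analysis plan that is not shown may supply the covariates. This stands in part: a reader might infer that the plan rules out adjustment, and the text does not say so. But the section names an estimator and defends it, and its plain reading is a comparison of two arm means.

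Three other readings go further than the document supports.
- That the economic result would be biased. Under randomisation chance imbalance is not bias, and a valid unadjusted SE already includes it.
- That the effectiveness analysis removes an imbalance which the economic analysis keeps, so that the economic section alone creates two different SDQ effects. The effectiveness section plans unadjusted and adjusted analyses and ranks neither first, so two estimates will exist anyway.
- That the economic analysis ignores school clustering. The section is silent on this, and silence does not show it.

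It is also fair to say that the gain cannot be sized from the document. It is small at r = 0.2, and stratification by deprivation, location and key stage already limits imbalance to the extent that these factors predict the outcome. Nor should the gain be expressed as extra children per class. With schools fixed and ICC 0.15, the variance per school cannot fall below 0.15 from 0.195, a cut of at most 23%.

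**Conclusion.** The point holds as a worthwhile improvement in method. The economic section specifies arm-mean comparisons without a baseline covariate, although the relevant T0 measures are collected and baseline adjustment is planned for effectiveness. The consequence is lost precision in incremental cost, incremental effect and the acceptability curves. The unadjusted interval would be about 2%, 9% or 25% wider at r of 0.2, 0.4 or 0.6. Those correlations are assumptions, and for the SDQ the change of rater makes the lower values more plausible. Confidence is good that no adjustment is stated, and moderate that none is intended. The stated 85% power for the primary outcome is unaffected.

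**What to change.** In Cost and cost effectiveness:
- Estimate incremental cost by regression adjusted for T0 cost, cohort and the stratification factors (school deprivation, city or non-city location, key stage).
- Estimate the T3 SDQ effect adjusted for T0 SDQ, cohort and the same factors, using the covariates of the adjusted effectiveness model so that the two adjusted T3 effects agree.
- Fit the net-benefit regression with the same covariates, and derive the acceptability curves from a bootstrap of that adjusted model.
- Allow for school clustering, as the effectiveness section does with random school effects, for example by resampling whole schools in the bootstrap.
- Keep the unadjusted difference in mean costs and effects as a descriptive line.

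The cost is a few lines of text in the economic analysis plan. No new data, visits or participants are needed, and inference stays on the arithmetic mean, as the article wants.

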#### *Qualitative analysis*

All audio-taped qualitative data will be transcribed verbatim and anonymised. Data will be stored using Nvivo software http://www.qsrinternational.com/products_nvivo.aspx and will be password protected. Analysis will be guided by a realist perspective, to identify experiences as the lived ‘reality’ of participants, but we are also interested in the ways in which participants account for their experiences within the context of the trial and their own schools based experiences [58]. Thematic analysis of interview and focus group data will be both theoretically driven by the research questions and allow for more inductive analysis whereby emergent themes are also identified. This mixed approach will help explicate patterns of experience and views of teachers, head-teachers and SENCos. As highlighted previously, analytical interests in the study vary across the different trial data collection periods. During the first year, analysis will focus on the research processes (teachers and head-teachers), while during the last two years, the focus will on the TCM intervention, use in the classroom including identification of key contexts, influences and transference (teachers, head-teachers and SENCos). Analytical focus within the year following TCM course completion will be on maintenance of TCM skills in the classroom and differentials in use of services.

In our analysis, ‘keyness’ of themes does not relate to incidence of occurrence but to whether a theme captures information relevant to the research questions, in this case relating to a range of trial processes [59]. The Framework Approach [36] will be used to manage data and aid systematic analysis (description and summary of key themes, patterns and links in the data), allowing the researcher to move between levels of abstraction during analysis and between a theory driven and more inductive approach, while also displaying the relevant data sources. This approach will help maintain a focus on the process evaluation objectives for the different phases of the study.

Summary and illustrative data will be available, relevant to the aims of the qualitative research for each phase, to facilitate further interpretation and discussion of which processes worked well or not so well within the main trial. A number of methods will be adopted to enhance rigour during analysis including: checks for thematic saturation and consistency [37]; shared analysis; analytical discussions will be recorded; self-reflective memos will also be kept by researchers [60,61] and we will undertake a deviant case analysis, which involves a re-interrogation of data searching for new themes not covered in the initial data analysis [61].

## Plan of investigation

### Recruitment

There are 67 primary schools in Plymouth, 31 in Torbay and 314 in Devon (total 412), which provide plenty of opportunity to recruit the 80 schools required for the trial. The recruitment of schools will be staggered over a three year period, with 15 schools recruited in the first cohort, 30 schools in the second cohort and 35 schools in the third cohort. A recruitment strategy will be devised, and recruitment targets and rates continually monitored to ensure adherence to the trial plan. The Devon, Plymouth and Torbay Associations of Primary Headteachers are supporting the study and are taking an active role in publicising the study to their members.

### Retention

Our calculations indicate that even if as many as six schools (clusters) from each arm withdrew from the study (i.e. we retained 34 in each arm) then the study would still have 80% power at the 5% level of significance to detect our specified effect of 0.3 standard deviations on the total SDQ difficulties score. In order to maximise retention, we will update participating schools, families and other key stakeholders about the study’s progress through termly newsletters as well as feeding into the newsletters of relevant organisations such as the Devon, Plymouth and Torbay Associations of Primary Head Teachers. Parents will be offered a voucher in recognition of their time spent on the completion of questionnaires and interviews and control teachers will be offered TCM if they provide data at T0 and T1. Teachers will also be offered incentives for questionnaire completion at each data collection point. As a result of feedback from our first Feasibility Study, we will recommend that head teachers do not nominate teachers who have additional management roles that may compete with TCM for time away from the classroom. The upper age limit of recruitment in Year 4 classes means that the follow-ups can be completed while even the older children remain at their primary school. In order to make their participation in the study as straightforward as possible and resolve any issues quickly, each school will have a named researcher to build a collaborative relationship.

### Data management

All confidential data will be held in accordance with the Data Protection Act. Each school and participant included in the trial will be assigned a unique identifier and all data will be stored without identifying details. Data will be held on a secure database on a password-protected computer at the Peninsula Medical School. Access to data will be restricted to the research team. All trial documentation will be retained for ten years. The Peninsula Clinical Trials Unit (PenCTU) will develop the study database in addition to carrying out randomisation. It is envisaged that the teachers will complete the questionnaire measures on themselves and the children using a web-based tool, which will also be designed and maintained by the PenCTU.

### Project timetable and milestones

The timing of recruitment, assessment of participants and delivery of the intervention is dictated by the school academic year between September and July. Milestones for the trial have been set according to this criteria and a rolling programme of recruitment will take place over three academic years. Three cohorts of schools will be recruited over the first three years of the study. Follow-up of these cohorts will overlap with recruitment and will take place between the second and fifth years of the study. Data entry and process evaluation will be ongoing, and economic evaluation and analysis will take place between the second and fifth years of the study. The trial data analysis and report writing will take place during the fifth year.

## Study management

STARS will be managed by a core research team who will meet weekly to review progress and manage the data collection and data entry (TF, VE and research workers). There will be three main management committees:

### Trial management group

The senior management team (TF, SL, SB, OU, SS, BN, VE) will meet on a bi-monthly basis to review progress and set targets.

### Trial steering committee (TSC)

The TSC will be chaired by [name], a clinical psychologist who has led several trials of interventions in schools, and will also include members of our User Advisory Group with representatives from specialist educational professionals, teachers and parents. The TSC will meet at the beginning of the trial and annually thereafter to oversee its conduct.

### Data monitoring and ethics committee (DMEC)

An independent DMEC will consist of an independent statistician (Chair), a mental health and/or educational practitioner and an academic researcher. The DMEC will meet annually and if necessary in response to any serious untoward incidents to ensure that recruitment and retention is sufficient for the trial to continue and to review the analytic plan. The DMEC will report to the TSC in the first instance.

The University of Exeter will act as the Sponsor for the study. STARS will be hosted in the Child Health Research Group, which has experience in the successful delivery of community based paediatric trials.

## User advisory group

User involvement has been essential at all stages of the design, planning and implementation of the STARS programme of work. A User Advisory Group (UAG) has been established comprising parents, teachers, head teachers, behavioural support staff and TCM group leaders. Formal meetings have been held during the design stage of the study with much additional informal contact between meetings providing an iterative process of study development. The UAG has provided essential advice on acceptability of the study to parents and teachers, as well as recruitment and data collection procedures.

